## Methods/design

### Study design and setting

The study is experimental and will be based on a Non-Randomised, non-blinded Controlled Trial including two groups: a) A Comparison group, which will receive the standard treatment at the clinical setting, including medical assessment, dietary and PA counselling every 3 months, with access to a 12-month programme including weekly IS and PA sessions and holiday camps; b) An experimental group which, in addition to the standard treatment, will have access, together with a peer of their choice, to a 12-month programme including weekly IS and PA sessions and holiday camps. The adolescents will be allocated to the groups according to the existence or not of peers of their choice to escort them in the intervention.

The setting of the study will be an Exercise and Health University Study Centre and the Paediatric Obesity Outpatient Clinic at Hospital Santa Maria (HSM). All participants will be recruited in the Lisbon region, Portugal (Figure 1).

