**Methods/design:**

The study is a non-randomised, non-blinded controlled trial, including two groups: 1) Comparison group (n = 35), which will receive a 12 month standard treatment at the hospital setting plus a weekly interactive and physical activity session; 2) Experimental group (n = 99), which will receive the standardized treatment at the hospital plus a weekly session together with a peer of their choice. The sample size calculations for the primary outcomes showed that we will have power to detect effect sizes of 0.25. Measures include: a) Dual-energy x-ray absorptiometry (for body composition assessment); b) Anthropometric evaluations; c) Assessment of physical activity levels by accelerometers; d) Psychosocial mediators (motivation and peer support) assessed with a package of psychometric questionnaires; and e) Outcomes (quality of life and well-being).

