## Background

Paediatric overweight and obesity have reached epidemic proportions in most industrialised countries [1]. In Portugal, a Southern European country with a traditional Mediterranean diet, the prevalence of overweight adolescents is among the highest in Europe. In a recent study [2], using a representative sample of Portuguese young people (22048 adolescents) aged between 10 and 18 years, there was an estimated prevalence of overweight and obesity of 23.1% and 9.6%, among girls and of 20.4% and 10.3% among boys, respectively. It was also seen that the prevalence of overweight and obesity decreases with age for boys and for girls from 13 to 18.

It is of the utmost importance to work on prevention to deal with this epidemic [3,4]. However, efforts must also be made to treat those young people who are already overweight [1,5]. There are several facts to support this need, in particular because adolescent obesity: a) has a significant impact on physical and psychosocial health [6]; b) is an independent risk factor for adult obesity [7]; c) is an independent risk factor for mortality in adults, perhaps more powerful than adult obesity itself [8]; and d) is a major threat to the sustained increase of life expectancy [9].

The psychosocial consequences represent the most prevalent co-morbidities associated with obesity [10]. Obese young people have low self-esteem (SE) and a reduced quality of life (QoL), mainly associated with their perceptions of physical appearance, athletic skills and social functioning [6]. There seems to be a dose–response association between the Body Mass Index (BMI) and a worse health related QoL in such a way that severely obese people have significantly higher values than those seen in people with a less severe degree of obesity [11]. Moreover, obese individuals show higher levels of body dissatisfaction [12] and higher levels of depression [13]. Body Image (BI) has been consistently identified as a protection factor against the development of risky behaviour associated with obesity [14].

Obese adolescents with low levels of self-esteem have shown significantly higher levels of sadness, loneliness and anxiety and are more susceptible to engage in experimental/risky behaviours [9], such as smoking or drinking [15]. Fonseca and Matos [16] showed that overweight adolescents find it harder to make new friends when compared with their peers who are not overweight.

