### Interactive sessions

Both the comparison and experimental groups will meet the intervention team once a week. These meetings are conducted with both groups, with the intervention being identical in its contents, since the differential factor is the presence or absence of the peer of choice. The joined session will last for about 120 minutes, covering contents on PA/exercise, nutrition and behavioural change in a context of small activity groups (including peers), using an experiential learning methodology, which consists of increasing one’s skills through transforming the experience [35].

The main objective is to bring the participants closer to independent decision making on their wish to make changes about their lifestyle and weight status (and how to do so), and subsequently help them to face the consequences of their choices, regardless of the results.

The participants are encouraged to discover situations in their daily lives that can be changed in order to increase the number of calories burnt by more than 2000 Kcal per week [39]. This can be achieved more formally (physical exercise in a guided context) or informally (PA). The University offered an exercise room that is available for daily use by the participants. Each participant will be given a pedometer to help monitor the number of steps taken each day. The use of pedometers has been associated with significant increases in PA and significant reductions in BMI [40].

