### Data collection

The variables will be assessed according to Table 1.

**Table 1 T1:** Variables, measures and timing of the data collection

**Parameters**	**Assessed through…**	**When**
IS attendance	Attendance sheets	IS
Frequency of exercise	Training plans and attendance records	IS and Exercise sessions
PA	Pedometers (OMRON Walking Style II, HJ-113-E) PA records (7-Day Physical Activity Recall)	IS/Holiday Camps
PA and Sedentary behaviour	Accelerometers (Actigraph GT3X)	0, 4, 8, 12, 24, 36 months
BMI	Weight (OMRON BF-500) SECA height stadiometer	
% Fat mass	Bioimpedance (OMRON BF-500)	
Body composition	Dual-energy X-ray absorptiometry, DEXA (QDR-1500; Hologic, Waltham, MA)	
Physical fitness	FITNESSGRAM test battery	
Caloric intake	Food records (4-day recall)	
Quality of Life	Impact of Weight on Quality of Life – Kids (IWQOL-kids) Kidscreen-27	
Well-being	Rosenberg Self-Esteem Scale (RSES) Body Image Assessment Questionnaire (BIA) Body Shape Questionnaire (BSQ)	
Peers	Perceptions of Parents Scales (POPS) – adapted to peers Self-Perception Profile for Adolescents (SPPA) – Social Acceptance Scales and “Best Friends”	
Self-regulation variables	Treatment Self-Regulation Scale (TRS) Locus of Causality for Exercise (LCE) Weigh Management Self-efficacy (WMSE) Behavioural Regulation in Exercise Questionnaire (BREQ-2) The Psychological Need Satisfaction in Exercise Scale (PNSE)	

Notes: IS – Interactive sessions; PA – Physical Activity.

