### Data analysis

We plan to use repeated measures analysis of variance to evaluate the impact of the intervention. Additionally, we plan to use structural equation models and/or multiple mediation analyses to assess the presence of predictors of the results of the intervention [58].

The intention-to-treat principle (last observation carried forward) will be followed for handling the missing data.

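### Groups are formed by whether the adolescent can bring a friend, and the stated analysis does not separate the peer effect from pre-existing social support and motivation

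*Protocol article*

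**What the plan says.** Under Study design and setting, the protocol article describes the trial this way: "The study is experimental and will be based on a Non-Randomised, non-blinded Controlled Trial including two groups". It then gives the allocation rule: adolescents are "allocated to the groups according to the existence or not of peers of their choice to escort them in the intervention". Those with a peer to bring enter the experimental group (n = 99 in the Abstract), and those without enter the comparison group (n = 35).

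Under Interactive sessions, the contents are the same for both groups, "since the differential factor is the presence or absence of the peer of choice".

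Under Data analysis: "We plan to use repeated measures analysis of variance to evaluate the impact of the intervention". No covariate, matching or weighting is mentioned. The same section adds "structural equation models and/or multiple mediation analyses to assess the presence of predictors of the results of the intervention". The Abstract gives motivation and peer support a single role: "Psychosocial mediators (motivation and peer support) assessed with a package of psychometric questionnaires".

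Table 1 lists peer scales (a peer-adapted POPS, and the SPPA social-acceptance and best-friend scales) and motivation scales (BREQ-2 among others). The timing cell, read as a merged cell covering these rows, starts at month 0. The Discussion does not mention selection or confounding.

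**The concern.** The group variable and the adolescent's prior peer situation are the same variable. Adolescents with no friend to bring are all in one group, and those with a willing friend are all in the other. The authors' own rationale makes this relevant to outcome. The Background reports that "overweight adolescents find it harder to make new friends when compared with their peers who are not overweight" and links low self-esteem in obese adolescents to loneliness. It also says adolescents' health behaviour is associated with that of their peers.

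If adolescents with a willing friend start with more support or stronger motivation, and those traits affect how weight, fat mass or activity change over a year, the groups will diverge even if the peer's attendance does nothing. The planned analysis would count that divergence as intervention effect. The mediation analysis has the same weakness: peer support at baseline is close to the allocation rule itself, so a path through peer support may partly reproduce how the groups were formed.

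**Working it through.** **The plan's own figure.** Sample size calculations states power 0.90 for an effect size of 0.25 with 134 participants, two-sided 5%, falling to 0.82 after 25% attrition. Reading 0.25 as Cohen's f for the between-group test, λ = N·f²·m / (1 + (m − 1)ρ). The number of measurements m and correlation ρ are not stated; I assume m = 2 and ρ = 0.5.
- N = 134: λ = 134 × 0.0625 × 2 / 1.5 = 11.17, power 0.913.
- N = 100 to 101: λ = 8.33 to 8.42, power 0.816 to 0.819.

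The figures can be reproduced. They presuppose comparable groups, so they say nothing about confounding.

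**What the test removes.** A trait that shifts the outcome by a constant amount at every visit cancels in the group-by-time contrast. A trait that is related to change does not cancel.

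**Size of the bias with no true peer effect.** Let g be the baseline gap between groups on the trait, in SD, and r its correlation with change in outcome. Neither is in the document; both are assumptions.
- Spurious effect b = g × r, in SD of change.
- Noncentrality δ = b × √(99 × 35 / 134) = b × √25.86 = b × 5.085.
- Rejection rate = Φ(−1.96 + δ) + Φ(−1.96 − δ).

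| g | r | b | δ | Rejection, formula | Rejection, simulation (1,500 runs) |
|---|---|---|---|---|---|
| 0.3 | 0.2 | 0.06 | 0.305 | 6.1% | about 7% |
| 0.5 | 0.3 | 0.15 | 0.763 | 11.9% | 11% |
| 0.5 | 0.5 | 0.25 | 1.271 | 24.6% | 24–25% |
| 0.8 | 0.5 | 0.40 | 2.034 | 53.0% | 54% |

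The first-row gap between formula and simulation is within simulation error: √(0.07 × 0.93 / 1,500) = 0.7 percentage points.

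**Scale.** The document does not state the metric of its effect size. As a standardised mean difference, 0.25 would be matched by the third row's spurious effect alone. As Cohen's f with a 99:35 split, it corresponds to 0.25 / √(99 × 35 / 134²) = 0.57 SD, which is above every row.

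**What adjustment achieves.** In the simulation, adjusting for a perfectly measured baseline trait brings the bias to about zero and the rejection rate to 4–6%. If the score has reliability 0.7 (assumed), the residual is (1 − 0.7) × g × r, or 0.02 to 0.12 SD over the four rows. Adding a more extreme case (g = 1.0, r = 0.5) takes it to 0.15 SD. Simulated rejection over that wider set is 4–11%. This covers only traits that are measured.

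**The case against.** The strongest reply is that the article does not say the ANOVA is unadjusted. Repeated-measures ANOVA can carry covariates, and a covariate list is often left to a fuller protocol or SAP, neither of which is shown. A reader might infer a plan limited to group and time; the document does not say that. The allocation rule, however, is fixed here. The one named impact analysis comes with no stated control, and motivation and peer support are given a mediator role, which does not control their baseline values. Structural equation models for predictors could include baseline traits, but confounding control is not their stated purpose.

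The design is also openly labelled non-randomised and non-blinded, so nothing is concealed. That discloses the problem without handling it.

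Third, a reader might infer that the groups will certainly differ, including on obesity severity or recruitment source. The document does not support this. The Background sentence on friendship compares overweight adolescents with others, whereas every participant is at or above the 95th percentile, so it shows no gradient within the trial. Nothing links school or clinic referral to having a peer. The cited finding that a friend's presence raises motivation describes the intended mechanism, not a baseline difference. A gap in social support is likely because the rule selects on it; a gap in motivation is plausible.

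Finally, the peer contrast is not the whole aim. The Objective section puts programme development and assessment first, and its second objective joins peers with increased exposure. The peer's presence is nevertheless the only stated difference between the groups.

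**Conclusion.** The point holds as a likely confounding of the between-group contrast that the stated analysis does not address. The mechanism follows from the allocation rule and the named method. The size does not: 0.06 to 0.40 SD, with 6–7% to 53% rejection under no true effect, rests wholly on assumed gaps and correlations. At the mild end the 5% level is barely disturbed, so it would be wrong to say that the test must fail badly.

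A reader might also infer that covariate adjustment settles the matter. It does not. Having a willing peer determines the group, so there is no overlap on that variable, and neither regression nor weighting can balance it. Adjustment can only reduce the part carried by measured traits.

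**What to change.** Make the primary between-group analysis a repeated-measures mixed model adjusted for a short, prespecified set of month-0 covariates:
- baseline value of the outcome, age, sex, cohort and recruitment source;
- one SPPA score (social acceptance or best friend);
- one motivation score, such as BREQ-2.

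With three cohorts this uses 1 + 1 + 1 + 2 + 1 + 1 + 1 = 8 degrees of freedom. Add two sensitivity analyses: propensity-score weighting on the same variables, and an analysis of change without adjustment for the baseline outcome, since the two approaches can disagree when groups are not randomised. State in advance that the group difference is an adjusted association and not a causal peer effect, and say why. Apply the same caution to mediation through peer support.

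The cost is small. The questionnaires are already in Table 1, and the remaining covariates are basic enrolment facts. A few degrees of freedom are spent, which matters with 35 comparison participants and is the reason to keep the list short. The conclusion becomes more cautious. Randomising peer attendance among adolescents who can name a peer would answer the causal question, but that is a different trial and not a condition for this correction.

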### Ethics approval and registration of the trial

The Ethics Committee of Faculdade de Medicina de Lisboa, University of Lisbon, approved this study, with the number 092/2013. Written consent will be obtained from both the adolescents and their parents or legal care providers. The study is registered in clinicaltrials.gov with the number NCT02024061.

**Figure 1 F1:**
[figure not shown]
Study design.

### Participants

The participants will be randomly selected from two origins: the Paediatric Obesity Clinic at HSM and schools in the Lisbon region. Adolescents from the schools will be identified as obese by their Physical Education teacher based on their BMI percentile [39], and referred to the HSM Clinic for further assessment before being included in the study.

### Sample size calculations

To calculate the sample size we focused on the primary outcomes, using two-tailed tests (p < 0.05), for a power of 0.90. For the projected sample (134), we estimate that the analyses will have a power to detect effect sizes of 0.25. Specifically, we estimate that our groups should be made up of: 99 participants, divided into 3 cohorts of 33 participants – experimental group; and two cohorts of 12 participants and one of 13, in the comparison group. We are aware that a lengthy intervention may result in an attrition rate of about 25%, so we are expecting a drop to 0.82 in the study’ power, if this attrition is observed.

### Eligibility criteria

Inclusion Criteria: Obese adolescents with a BMI greater than or equal to the 95^th^ percentile [39], aged between 14 and 17, with Caucasian origin, agreeing with the commitment.

Exclusion criteria: a) cognitive impairment; b) pregnancy; c) serious illnesses; d) other factors with contraindication for regular PA.

### Subject withdrawal

The following will give rise to the withdrawal of participants:

•Attendance less than 75% of the IS or PA sessions;

•Acute illness implying non-compliance with the planned sessions;

To ensure that the participants comply with the assumptions, records will be kept of the attendance at the IS and PA sessions. Participants will not be substituted.

### Intervention

The study comprises an experimental group and a standard treatment group. The intervention will be similar in both groups with the exception that in the experimental group every adolescent will be escorted by a peer of their choice at every moment of the intervention (IS, PA sessions and holiday camps). The multidisciplinary team is made up of physical activity specialists, nutritionists/dieticians, psychologists and paediatricians, all of them with previous training in adolescent obesity, resulting from their involvement in the Paediatric Obesity Clinic at HSM.

### Interactive sessions

Both the comparison and experimental groups will meet the intervention team once a week. These meetings are conducted with both groups, with the intervention being identical in its contents, since the differential factor is the presence or absence of the peer of choice. The joined session will last for about 120 minutes, covering contents on PA/exercise, nutrition and behavioural change in a context of small activity groups (including peers), using an experiential learning methodology, which consists of increasing one’s skills through transforming the experience [35].

The main objective is to bring the participants closer to independent decision making on their wish to make changes about their lifestyle and weight status (and how to do so), and subsequently help them to face the consequences of their choices, regardless of the results.

The participants are encouraged to discover situations in their daily lives that can be changed in order to increase the number of calories burnt by more than 2000 Kcal per week [39]. This can be achieved more formally (physical exercise in a guided context) or informally (PA). The University offered an exercise room that is available for daily use by the participants. Each participant will be given a pedometer to help monitor the number of steps taken each day. The use of pedometers has been associated with significant increases in PA and significant reductions in BMI [40].

The intervention is based on a group functioning rationale which, in accordance with the social contagion theory [33], may contribute to positively influence the different members of the group. Peer group influence is major at this age and it is expected that young people will be more active when they are accompanied by their peers and their friends [41]. Benefits arising from group work, in the context of obesity management, were obtained through improving social functioning, which was positively associated in dimensions related with self-concept [34]. This effect was also seen in a recent study [42], which was intended to assess a PA intervention based on the use of pedometers and provision of support material to peers. It has been shown that the best results were obtained in the group that received only peer support material and objectives to be reached with the use of the pedometers. Salvy and colleagues [41], in a study with 88 adolescents, showed that the presence of a friend increased the motivation to be physically active. The use of peer and/or family support material has been suggested as an effective mean of promoting PA in young people at risk of sedentary behaviours [43], both at the beginning of the maintenance phase [44], and as an ongoing source of support for improving psychosocial functioning [45].

The IS included a variety of challenging physical activities, support provision for definition of a structured training plan, adjustment of daily tasks according to an active lifestyle, reduction/modification of sedentary behaviour strategies (e.g. reduction of screen time), help in discovering the preferred type of activity overcoming some myths and barriers around exercise/PA, and support in ambivalent behaviour. Because PA is the main modifiable component associated with energy expenditure in the energy balance equation [39], various international organisations have looked at PA promotion as a crucial modifiable health behaviour [46].

In addition to encouraging PA, it is equally important to reduce/modify sedentary behaviour [39,47]. Tremblay et al. [48], in a systematic literature review, showed that over 2 hours of television a day was associated with an unfavourable body composition, less physical aptitude, lower self-esteem values and more maladjusted social behaviour. According to the Canadian Sedentary Behaviour Guidelines for Children (5-11 y) and Youth (12-17 y) recently launched, it is recommended that for health reasons, children and adolescents should reduce daily sedentary time, by means of limiting screen time to a maximum of 2 hours a day, avoiding motorised transportation, along with the reduction of sitting time and time spent “inside the house” [49].

The IS also seek to provide self-regulation strategies for diet/nutrition behaviour improvement through providing information focused on increased awareness about nutritional facts; negotiating the modification of dietary patterns [50]; and using the food traffic light [51]. According to the recommendations of Spear et al. [39] and Davis et al. [52], there will be a focus on learning specific strategies/skills which include the importance of breakfast; increasing the number of meals during the day; avoiding hunger and unregulated consumption; reducing emotional (compulsive) and/or distracted eating; eating according to energy needs; consumption of food with a high satiety index; reduction in food consumption rich in animal fat; increase in the consumption of fruit, vegetables, cereals and other fibre rich foods; reduction in sugar consumption; limited consumption of drinks and fast food; lower portions size; and learning how to read and understand food labels.

With regard to cognitive-behavioural modification, the focus will be on the identification of problems and face the difficulties that arise during the programme. As there is nothing more central to behaviour than motivation, the whole interaction will be self-motivation and self-regulation centred, seeking to identify personal resistance and barriers, developing skills for prevention, identification and overcome [52]. Specific strategies [39] will include: the increase in self-efficacy through analysing and overcoming typical barriers such as lack of time, skill or accessibility; making planning more flexible; positively accepting failures, and/or that change is neither quick nor easy; building a system of incentives; and defining realistic, tangible objectives.

